#### **4.2.2 Secondary Outcome Measure**

- Volume of secretions (increased or decreased may be beneficial)
- Work of breathing
- Airway resistance
- Number of additional nebulised doses of saline or other drugs administered during the study period
- Ease of sampling, in opinion of treating nurse
- Frequency of requiring changing the HME filter
- Length of time on ventilator
- Length of stay in ICU
- ICU Mortality

### **4.3 Laboratory Tests**

The patient will have no additional blood tests as part of the study.

## **5. ASSESSMENT OF SAFETY**

Throughout the duration of the study period the recruited patients will be closely monitored by a Intensive Care Nurses and critical care physicians. They will have continuous monitoring of their oxygen saturations (SpO2), heart rate, with regular monitoring of blood pressure. As part of standard care patients will have regular monitoring of their ventilator parameters including the tidal volume being delivered and airway pressures.

The treating clinician can stop the nebulisation if at any point they have clinical concern and institute any rescue therapy deemed necessary.

## **6. PHARMACOVIGILANCE**

### **6.1 Definitions of adverse events**

#### **Adverse Event (AE)**

AEs can be defined as any untoward medical occurrence in a patient or other clinical investigation participant taking part in a trial of a medical device, which does not necessarily have to have a causal relationship with the device under investigation.

An AE can therefore be any unfavourable and unintended sign (including an abnormal laboratory finding), symptom or disease temporally associated with the use of the device, whether or not considered related to the device.

Adverse events that are study related and not complications of nebulisation are hard to identify. Anticipated adverse events/complications that can occur with any nebulisation are bronchospasm, accumulation of fluid in the circuit, feeling of chest tightness.

These will all be documented on AE report forms and reported to the Chief Investigator.

### **6.2 Serious Adverse Event (SAE)**

SAE is an adverse event that

- Led to death
- Led to serious deterioration in the health of the subject that:
  - Resulted in a life-threatening illness or injury
  - Resulted in a permanent impairment of a body structure or a body function
  - Required in-patient hospitalisation or prolongation of existing hospitalisation
  - Resulted in medical or surgical intervention to prevent permanent impairment to a body structure or a body function

SAEs are not expected due to the trial, but the investigators are aware that SAEs may occur from nebulisation.

### **6.3 Serious Adverse Device Events (SADE)**

A serious adverse device effect (SADE) is any untoward medical occurrence seen in a patient that can be attributed wholly or partly to the device which resulted in any characteristics of a serious adverse event.

SADE is also any event that may have led to these consequences if suitable action had not been taken or intervention had not been made or if circumstances had been less opportune. All cases judged by either the reporting medically qualified professional or the sponsor.

#### **6.4 Reporting and documentation of complications, and adverse device effects.**

Complications and Adverse Events will be documented on Adverse Event Report forms for the duration of the investigation. Furthermore, the outcome of such complications will be documented and any changes in outcome updated during the study. Each complication and adverse event must be assessed for seriousness, causality and expectedness against the expected complications resulting from both the surgical procedure and the use of the medical device(s). All complications will be reported to the Chief Investigator.

#### **6.5 Reporting of serious adverse events to the Sponsor.**

The following events are considered reportable to the sponsor.

- Any Serious Adverse Event that is considered related to the surgical procedure, trial specific procedures, or the medical device(s) that is considered unexpected by the Chief Investigator or their delegate.
- Any device related serious adverse event that led or may have led to one of the following outcomes:
  - The death of a patient
  - A serious deterioration in the health of a patient.

A serious deterioration in health may include (non-exhaustive):

- a) Life threatening illness
- b) Permanent impairment of a body function or permanent damage to a body structure
- c) A condition necessitating medical/surgical intervention to prevent a) or b)
- d) Foetal distress or death, or any congenital anomalies or birth defects.

All SAEs meeting the above criteria must be reported to the Pharmacovigilance Office immediately (within 24 hours) using the SAE form for a CE Marked Medical Device. The SAE form should be completed and signed by appropriately delegated staff. The form should be faxed or e-mailed to the PV Office ([[contact]](mailto:[contact])) and a copy placed in the Study Site File. If necessary, a verbal report can be given by contacting the PV Office on [name]. This must be followed up as soon as possible with a signed written (or electronic) report.

If all of the required information is not available at the time of initial reporting, the CI (or designee) must ensure that any missing information is forwarded to the PV Office as soon as this becomes available. The report should indicate that this information is follow-up information for a previously reported event.

## **6.6 Reporting of related and unexpected events to the REC**

The Sponsor will report all RUSAEs to the ethics committee within 15 days of the PV office becoming aware of the event, via the 'report of serious adverse event form' for non-CTIMPs published on the Health Research Authority web site.

<http://www.hra.nhs.uk/documents/2015/02/safety-report-form-non-ctimp.docx>. The form should be completed in typescript and signed by the Chief Investigator.

## **7. STATISTICS AND DATA ANALYSIS**

### **7.1 Statistical analysis plan**

A total of 60 patients will allow us to determine the distribution of the primary and secondary outcome measures which will provide information to power a further clinical study. Since this is a pilot study, we are not powered to formally compare differences between the treatment groups.

### **7.2 Primary efficacy analysis**

A median reduction in the sputum viscosity by 0.5 on a pourability scale for respiratory sections between the three humidification methods tested.

### **7.3 Secondary efficacy analysis**

- Volume of secretions (increased or decreased may be beneficial)
- Work of breathing
- Airway resistance
- Number of additional nebulised doses of saline or other drugs administered during the study period
- Ease of sampling, in opinion of treating nurse
- Frequency of requiring changing the HME filter
- Length of time on ventilator
- Length of stay in ICU
- ICU Mortality

### **7.4 Safety analysis**

The safety data (adverse events) – both numbers of subjects and events – will be summarised by randomised group and overall using descriptive statistics. No formal statistical tests comparing the randomised groups will be pre-specified. Adverse event will be reported to GGC and the local ethic committee annually and required by Scottish Research Governance Standards.

### **7.5 Software for statistical analysis**

The statistical software to be used will be SPSS, release 19.0 for Windows; SPSS, Chicago, IL

## **7.6 Sample size**

This is a pilot feasibility study and a total of 20 patients in each group is adequate to provide information to power a definitive study. The chosen samples sizes can be further justified as follows:

We will determine if the primary end point (viscosity even you are looking at the change in the score from baseline to final measurement, assuming the score is 1 to 4 in 0.5 increments at each time point, the distribution in values of change could range from -3 to +3 in 0.5 increments. This can therefore be treated as a continuous measurement. With 20 subjects we estimate an 80% power to detect a difference between any 2 groups of 0.503 per standard deviation (effect size=0.503) for the change in score. This assumes a significance level (p value) of 0.0167 to take into account that we would use 3 comparisons:

1. (Intermittent standard nebulisation vs. Continuous Aerogen nebulisation,
2. Intermittent standard nebulisation vs. Intermittent Aerogen nebulisation,
3. Continuous Aerogen nebulisation vs. Intermittent Aerogen nebulisation)

The statistically analysis and powering of this study were based on advice for [name] senior statistician the Robertson Centre, 24th July 2019.

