## **3. STUDY DESIGN**

### **3.1 Study Population**

A total of 60 patients will be recruited to the study. Each patient will be randomised to receive:

Continuous nebulisation of 0.9% normal saline using the Aerogen Solo Nebuliser (50mls/24h via a syringe feed set) OR

Intermittent nebulisation of 0.9% normal saline using the Aerogen Solo Nebuliser (5mls, 6 hourly) OR

Intermittent standard nebulisation of 0.9% normal saline using the Intersurgical Cirrus 2 self-sealing Jet Nebuliser (5 mls, 6 hourly)

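### Section 7.6 claims 80% power at 0.503 SD with 20 per group and alpha 0.0167, but that design detects about 1.06 SD and has about 19% power at 0.503 SD

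*Protocol*

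**What the plan says.** Section 7.6 first gives a pilot rationale, that "a total of 20 patients in each group is adequate to provide information to power a definitive study", and then offers a power calculation as further justification of the sample size. The endpoint is the change in pourability score from baseline to final measurement. The section notes that "the distribution in values of change could range from -3 to +3 in 0.5 increments" and concludes: "This can therefore be treated as a continuous measurement". The power statement follows: "With 20 subjects we estimate an 80% power to detect a difference between any 2 groups of 0.503 per standard deviation (effect size=0.503"). On alpha it says: "This assumes a significance level (p value) of 0.0167 to take into account that we would use 3 comparisons". It lists the three comparisons, which are all the pairs among the three arms.

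Two other sections bear on the point. Section 7.1 says that, because this is a pilot, "we are not powered to formally compare differences between the treatment groups". Section 7.2 gives the primary efficacy target as "A median reduction in the sputum viscosity by 0.5 on a pourability scale".

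**The concern.** A half-SD difference between two groups of 20, tested at a Bonferroni-adjusted level, should not be detectable with 80% power. The stated figure therefore looked too small by a factor of about two. Every input needed for the check is printed in section 7.6 except the sidedness of the test. The effect is already in SD units, so no unstated SD is needed.

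Three uses of the figure are at stake.

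- **Reading the results.** The synopsis plans a Kruskal-Wallis comparison of viscosity, and section 17 expects the findings to help inform best practice, so group differences will be looked at. On the strength of 7.6, a non-significant pairwise result could be taken as evidence against half-SD differences.
- **Planning the next trial.** Section 7.1 gives the pilot's purpose as providing information to power a further study. If this calculation were carried forward, a half-SD target would appear to need 20 per group.
- **Consistency.** Sections 7.1 and 7.6 make opposite statements about whether the groups can be compared with adequate power.

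**Working it through.** **Inputs**

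| Input | Value | Source |
|---|---|---|
| Patients per group | 20 (60 in three arms) | Sections 7.6 and 3.1 |
| Alpha per comparison | 0.0167 (0.05/3) | Section 7.6 |
| Power | 0.80 | Section 7.6 |
| Difference between two groups | 0.503 SD | Section 7.6 |
| Test and sidedness | Not stated; two-sided two-sample t-test assumed, one-sided also tried | Assumption |

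**Step 1. Detectable difference, normal approximation**

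d = (z for alpha/2 + z for power) × √(2/n)

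z for alpha/2 at 0.0167 = 2.393; z for 80% power = 0.842; √(2/20) = 0.3162.

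d = (2.393 + 0.842) × 0.3162 = 1.02 SD.

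The exact noncentral t calculation (38 df) gives **1.063 SD**. This does not reproduce 0.503.

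**Step 2. Power at 0.503 SD**

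Noncentrality = 0.503 / 0.3162 = 1.591.

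- Normal approximation: Φ(1.591 − 2.393) = Φ(−0.802) = 21.1%.
- Noncentral t: **19.4%**.
- Simulation (200,000 runs): 19.3%.

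**Step 3. Patients needed for 80% power at 0.503 SD**

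n = 2 × [(2.393 + 0.842) / 0.503]² = 82.7, so 83 per group. The t-test version gives 84.2, so **85 per group**, or 3 × 85 = 255 in three arms against 60 planned.

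**Step 4. Does another reading give 0.503?**

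Two-group comparison of means, 20 per group (noncentral t):

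| Alpha and sidedness | Detectable difference at 80% power | Power at 0.503 SD |
|---|---|---|
| 0.0167 two-sided | 1.063 SD | 19.4% |
| 0.0167 one-sided | 0.968 SD | 28.0% |
| 0.05 two-sided | 0.909 SD | 34.1% |
| 0.05 one-sided | 0.801 SD | 46.7% |

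Other variants at two-sided alpha 0.0167:

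| Variant | Detectable effect at 80% power |
|---|---|
| Pairwise contrast with error pooled over three arms (57 df) | 1.05 SD |
| Mann-Whitney, relative efficiency 0.955 | 1.09 SD |
| One-sample or paired, n = 20 | 0.783 SD |
| 40 per group | 0.737 SD |
| 60 per group | 0.598 SD |
| Cohen's f, two groups, N = 40 | f = 0.532 (power at f = 0.503 is 74.8%) |
| Cohen's f, three groups, N = 60 | f = 0.474 (power at f = 0.503 is 85.3%) |

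None of these gives 80% power at 0.503 with the stated inputs.

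**Step 5. In pourability grades**

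The protocol gives no SD for the change in score, so the 0.5-grade figure of section 7.2 can only be turned into a condition on that SD.

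- With the correct figure: 0.5 / 1.063 = 0.47. A mean difference of 0.5 grade has 80% power only if the SD of change is at most about 0.47 grade.
- With the stated figure: 0.5 / 0.503 = 0.99. An SD of about 1.0 grade would appear to be enough.

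This is an approximation, because section 7.2 speaks of a median and the synopsis plans a rank test. The Mann-Whitney figure of 1.09 SD would make the condition slightly tighter.

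**The case against.** **The sample size does not rest on this sentence.** Section 7.6 leads with the pilot rationale and adds the power statement only as further justification, while section 7.1 disclaims formal comparison. No stopping, futility or equivalence decision uses 0.503. All of this is true. It means that 60 patients need not change, and that the harm lies in how the figure may be read or re-used. It does not make the figure right, and 7.1 contradicts the claim in 7.6 without correcting it.

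**The 0.503 may be a mislabelled metric.** For two groups, Cohen's f is half the standardised difference. If 0.503 were an f, the difference would be 2 × 0.503 = 1.006 SD and power about 75%, so the underlying calculation would be close to the design's real sensitivity. This is the most plausible kind of origin, but it does not rescue the text. At the stated alpha the two-group f is 0.532 (about 0.51 by normal approximation); an f of 0.504 appears only at two-sided alpha 0.025. Section 7.6 also describes 0.503 as a difference between two groups per standard deviation, which is not an f.

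**Sidedness and test are not stated.** This is fair, and the corrected text should name both. Under the one-sided reading the detectable difference is still 0.97 SD, so the conclusion is unchanged.

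**Conclusion.** The power statement in section 7.6 is wrong as written. Its detectable difference is too small by a factor of about two (0.503 against 1.06 SD), and its power is overstated about fourfold (80% against 19%). These figures assume a two-sided two-sample t-test, a common SD and all 20 patients per group evaluable. Relaxing the choice of sidedness, multiplicity adjustment or test does not bring a two-group comparison of 20 against 20 near 80% power at 0.503 SD; the most favourable case tried reaches 47%. The corrected figure agrees with section 7.1, so 7.6 is the text to change. The pilot rationale for 20 per group is unaffected.

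**What to change.** Replace the power sentence in section 7.6 with wording such as: *With 20 patients per group and a two-sided two-sample t-test at alpha 0.0167, a pairwise comparison has 80% power for a difference of about 1.06 SD in the change in score; power for a difference of 0.5 SD is about 19%.*

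Keep 60 patients on the pilot rationale of estimating the SD and distribution of the outcomes. State in 7.6, as 7.1 already does, that the pairwise comparisons are not adequately powered. If 0.503 came from a different metric or software setting, the sponsor's statistician should identify it and state the result as a between-group difference in SD units.

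The cost is a protocol wording amendment. The stated sensitivity becomes less favourable. The number of patients, the endpoint, the test and the study procedures do not change.

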| Duration of Treatment:                  | Up to 72 hours                                                                                                                                                                                                                                                                                                                                                                             |
| Product, Dose, Modes of Administration: | 
Continuous nebulisation of 0.9% normal saline using the Aerogen Solo Nebuliser (50mls/24h via a syringe feed set)
OR
 
Intermittent nebulisation of 0.9% normal saline using the Aerogen Solo Nebuliser (5mls, 6 hourly) OR
 
Intermittent standard nebulisation using the Intersurgical Cirrus 2 self sealing Jet Nebuliser (5 mls, 6 hourly)
                        |
| Statistical Analysis:                   | Comparison of the difference in the viscosity of respiratory sections compared using Kruskal Wallis test with SPSS, release 19.0 for Windows; SPSS , Chicago, IL                                                                                                                                                                                                             |

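### The protocol's statements on the primary comparison are unreconciled: no formal comparison (7.1), 80% pairwise power at 0.0167 (7.6), a Kruskal-Wallis test (synopsis) and a bare 0.5 median gap (7.2)

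*Protocol*

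**What the plan says.** Four places in the protocol bear on how the three arms are compared on pourability.

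- **Synopsis, Statistical Analysis:** the difference in viscosity is "compared using Kruskal Wallis test". No significance level or follow-up step is given.
- **Section 7.1:** because this is a pilot, "we are not powered to formally compare differences between the treatment groups".
- **Section 7.2:** the entire primary efficacy analysis reads "A median reduction in the sputum viscosity by 0.5 on a pourability scale for respiratory sections between the three humidification methods tested". There is no test, interval or error rate.
- **Section 7.6:** the sample size is first justified on pilot grounds: "a total of 20 patients in each group is adequate to provide information to power a definitive study". A power statement follows: "With 20 subjects we estimate an 80% power to detect a difference between any 2 groups of 0.503 per standard deviation". The level is explained by "This assumes a significance level (p value) of 0.0167 to take into account that we would use 3 comparisons", and the three pairwise contrasts are listed.

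Section 7.7 refers to a pre-specified SAP, which is not available here.

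**The concern.** Sections 7.1 and 7.6 cannot both stand. A study that cannot support formal comparisons does not have 80% power for each of three multiplicity-adjusted comparisons.

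Section 7.2 puts a threshold where an analysis belongs. It does not say whether 0.5 is a difference worth detecting or a result that would count as efficacy. The scale moves in half grades, so 0.5 is a single step, and medians of 20 half-step scores can easily differ by one step through chance.

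With no stated order among the threshold, the global test and the three pairwise tests, what is reported as the primary result could depend on which section the analyst follows.

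**Working it through.** **Inputs.** From section 7.6: 20 per group, three groups, standardised difference d = 0.503, level 0.0167, power 80%. From section 7.2: a 0.5-grade gap. Two inputs are not given. Sidedness is taken as two-sided (one-sided also shown). The SD of the change score is assumed, over a range.

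**1. The significance level.** 0.05 / 3 = 0.0167. This reproduces.

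**2. The 80% power.** For two groups of n, power ≈ Φ(d·√(n/2) − z), where z = 2.393 is the two-sided critical value at 0.0167.

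- d·√(n/2) = 0.503 × √10 = 1.591, and 1.591 − 2.393 = −0.802, so power is 21.1%. With the noncentral t it is 19.4%.
- Detectable difference at 80% power: (2.393 + 0.842) × √(2/20) = 1.02 SD. With the t distribution it is 1.06 SD.
- Patients needed for d = 0.503: 2 × (3.235 / 0.503)² = 82.7, so 83 per group (85 with the t distribution), or 249 to 255 in total.
- Other readings do not recover 80%. A one-sided test gives 28–30%, and a paired or one-sample calculation with n = 20 gives 38%. The nearest is 0.503 read as Cohen's f for two groups, at 75%. That is not what the text describes.

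**3. The 0.5-grade difference at 0.0167.** Power depends on the unknown SD: 74% at SD 0.5, 36% at 0.75 and 19% at 1.0. It reaches 80% only if the SD is about 0.5 / 1.063 = 0.47.

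**4. The 0.5 gap used as a rule when no arm differs.** Simulation: 20 per arm, scores in half steps, 40,000 trials per SD.

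| Assumed SD | A given pair differs by ≥ 0.5 | Some pair differs by ≥ 0.5 |
|---|---|---|
| 0.5 | 8% | 13% |
| 0.75 | 26% | 42% |
| 1.0 | 39% | 62% |

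A separate simulation with 6,000 trials per scenario gave 12%, 43% and 61%. In that simulation, the gap was met in 10%, 37% and 57% of null trials while neither Kruskal-Wallis at 0.05 nor any pair at 0.0167 was significant. Kruskal-Wallis significant with no pair below 0.0167 was rarer: about 1% of null trials, and 3–5% where arms differed.

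**5. Two ways to organise the tests.** With three groups, any two pairwise nulls together imply that all three groups are equal. A global test at 0.05 followed by pairwise tests at 0.05 is therefore a closed procedure. Simulated familywise error under the global null was 4.8%, against 4.1% for Bonferroni. With one pair truly equal it stayed within 5%. Power for a truly different pair:

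| Pattern | Bonferroni 0.0167 | Kruskal-Wallis gate |
|---|---|---|
| One arm different by 0.503 SD | 17–18% | 23–24% |
| Equally spaced arms, extreme pair 0.503 SD | 17.7% | 22.0% |
| One arm different by 0.8 SD | 47% | 59% |
| One arm different by about 1.06 SD | 75% | 85% |
| Equally spaced arms, extreme pair 1.05 SD | 75.7% | 80.2% |

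Even an unadjusted t-test at 0.05 has only 34% power at 0.503 SD.

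**The case against.** The strongest reply is that nothing here is labelled a decision rule. The level in section 7.6 is a power assumption ("This assumes a significance level (p value) of 0.0167"), the 0.5 in section 7.2 may be a badly worded target difference, and a global test followed by Bonferroni pairwise tests is a familiar sequence. The order of testing could sit in the unseen SAP. This stands as far as it goes. A reader might infer that the protocol contains three incompatible decision rules, but the text does not support that. The omnibus and pairwise tests can coexist, and the fault is that the statements are not reconciled.

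It does not dispose of the point. A SAP cannot make sections 7.1 and 7.6 both true, and section 7.2 states its threshold under the heading of the primary efficacy analysis.

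A second reply is that Bonferroni at 0.0167 is valid, so replacing it is a preference. That is right: the split is not an error.

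A third is that the chance rates rest on assumed SDs, on 0.5 being used alone as a success rule (which section 7.2 does not say), and on one change score per patient. Section 4.2.1 instead takes a median change over all the 10:00 and 16:00 scores, whose variability is unknown. These limits are accepted. The rates show what would follow if the sentence were applied as a rule; they do not predict the trial's error rate.

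**Conclusion.** The point holds as a failure to reconcile, together with a wrong power figure.

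- Section 7.1 contradicts the power claim in section 7.6. The arithmetic favours section 7.1: power at 0.503 SD is about 19–21% (two-sided, equal groups of 20, no dropout), not 80%.
- Section 7.2 leaves the role of 0.5 open. As a stand-alone rule it would be met by chance in about 12–13%, 42% or 62% of null trials at assumed SDs of 0.5, 0.75 or 1.0.
- A reader might also infer that a better multiplicity procedure would rescue the power claim. It would not. At the protocol's own effect size with one arm different, the gated procedure moves power from about 17–18% to 23–24%. The larger gains occur at differences the protocol does not name.

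The pilot justification for 20 per group does not depend on the power claim and is unaffected.

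**What to change.** - **Section 7.2:** state that 0.5 grade is the difference of interest and not a success criterion. Make the primary result the three pairwise differences with 95% confidence intervals, labelled exploratory in line with section 7.1.
- **Section 7.6:** remove the 80% power claim and keep the pilot justification, or restate it: 20 per group at two-sided 0.0167 gives 80% power for about 1.06 SD.
- **Synopsis and section 7.6, if tests are reported:** name one procedure in both places. Bonferroni at 0.0167 is acceptable. Kruskal-Wallis at 0.05, followed only if significant by the three pairwise tests at 0.05, is also valid with three groups and usually more powerful. If the gated procedure is chosen, any restated power should refer to it.

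The cost is wording only, with no change to patients, visits or data. The gated procedure has one small price: no pair can be declared different when the global test misses 0.05. An unadjusted 95% interval may then still exclude zero, which is a further reason for the exploratory label.
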